## 12.3 Evaluation criteria

### 12.3.1 Fever

Fever is evaluated through body temperature, and is graded as following;

| Criteria   | Grade 0 | Grade 1 | Grade 2   | Grade 3 | Grade 4                |
|------------|---------|---------|-----------|---------|------------------------|
| Fever (°C) | none    | <38.7   | 38.7~40.0 | >40.0   | Fever with hypotension |

### 12.3.2 Subjective/objective sign

The severity of subjective/objective sign is evaluated in grade by pre-existing criteria (for example, WHO adverse event evaluation criteria) or by general evaluation criteria during researcher's physical examination.

| General evaluation criteria | None (0) | Mild (1) | Moderate (2) | Severe (3) |         |
|-----------------------------|----------|----------|--------------|------------|---------|
| WHO                         | Grade 0  | Grade 1  | Grade 2      | Grade 3    | Grade 4 |

- WHO 5 phase classification

Grade 0: Condition available of normal activity without any restraint

Grade 1: Condition possible of ambulation and work, but restrained from physically challenging activity.

Grade 2: Condition possible of ambulation and self-protection, but not possible to perform more than 50% of working hours

Grade 3: Condition possible of limited self-protection, and restricted to bed or chair for more than 50% of working hours

Grade 4: Condition impossible of self-protection, and completely restricted to bed or chair

- General criteria classification

Mild (1): Adverse event that is easily bearable.

Moderate (2): Adverse event that restrict daily life considerably

Severe (3): Adverse event that restricts normal daily life.

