## 6. Inclusion/exclusion criteria, target number of subjects and its estimation basis

### 6.1 Inclusion criteria

Patients are selected as subjects with following conditions;

- (1) Adult male/female patients aged from 18 to 80.
- (2) ICU patients who are hemodynamically unstable to be in need of CRRT and has one of the hemorrhagic tendencies described as follows.
  - ① Platelet < 100,000
  - ② aPTT > 60 sec
  - ③ PT-INR > 2.0
  - ④ Active bleeding
  - ⑤ Major surgery within 48 hours
  - ⑥ History of cerebral hemorrhage or major bleeding within 3 months
  - ⑦ Septic shock or DIC
- (3) Patients or his/her legal guardian has voluntarily agreed to participate in the study and provided written informed consent.

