## 12.2 Evaluation method

- Adverse event is newly developed symptom that was not observed before study enrollment, and is not intended symptom and sign that is transient related to the usage of the study medication, regardless of cause-and-effect relationship with the study medication.
- The undesirable clinical sign and symptom that was observed during or before screening is documented in physical examination data sheet, and is not documented as adverse events.
- The adverse event is thoroughly reported in the adverse event data sheet (symptom and sign, observation date, duration), and event that is not documented in the data sheet is considered as subjective symptom.
- The severity of adverse event is referred to evaluation criteria by the researcher and the severity is graded.
- The cause-and-effect relationship between the symptom and medication is referred to evaluation criteria and graded in 6 phases.

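### One of the two severity scales allowed for subjective and objective signs (Protocol 12.3.2) grades the patient's function, not the adverse event

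*Protocol*

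**What the plan says.** Section 12.2 requires grading: "The severity of adverse event is referred to evaluation criteria by the researcher and the severity is graded". Sections 8.2.13 and 12.5.1 also list severity among the items recorded for an adverse event.

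Section 12.3.2 supplies the criteria for signs other than fever and leaves a choice: "The severity of subjective/objective sign is evaluated in grade by pre-existing criteria (for example, WHO adverse event evaluation criteria) or by general evaluation criteria". It then prints both scales.

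- **WHO scale, grades 0 to 4.** Grade 0 is "Condition available of normal activity without any restraint", grade 3 is "Condition possible of limited self-protection, and restricted to bed or chair for more than 50% of working hours" and grade 4 is "Condition impossible of self-protection, and completely restricted to bed or chair". Grades 1 and 2 are likewise set by walking, working and self-care.
- **General scale, mild (1) to severe (3).** Mild is "Adverse event that is easily bearable" and moderate is "Adverse event that restrict daily life considerably". Severe says only that the event limits ordinary daily living, with no word of degree.

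A small table in the same section lines the two scales up, level 1 with grade 1, level 2 with grade 2 and level 3 with grade 3. WHO grade 4 has no counterpart.

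Section 6.1 defines the population as "ICU patients who are hemodynamically unstable to be in need of CRRT" with a haemorrhagic tendency. Section 4.3 states that the study is open label.

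**The concern.** A severity grade should change with the event and not with the condition of the patient who has it. The printed WHO grades are a performance-status scale. Section 12.2 keeps findings already present at screening out of the adverse event record, but a functional scale brings the patient's prior state back in through the grade.

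The general scale is the better of the two, because it speaks of the event. Its upper levels are nevertheless weak. Moderate carries a qualifier of degree and severe does not, so read literally the two are hardly ordered. Both also rest on daily life, which means little for a patient on CRRT in intensive care.

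Comparing safety between the arms is a stated aim (sections 3.1.2 and 7.1). If severity is recorded on a scale that reflects the patient, or on different scales for different events, the grades cannot be compared between patients or arms. Because the researcher knows the arm, the free choice of scale also leaves room for uneven grading. The document gives no sign that this would happen deliberately.

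**Working it through.** There is no figure in the plan to reproduce. The check sets the definitions against each other and against the population.

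**Step 1: what each definition describes.** Of the WHO grades, 5 of 5 describe the patient's function and 0 of 5 mention an adverse event. On the general scale, 3 of 3 definitions (mild, moderate, severe) describe the adverse event.

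**Step 2: two example patients.** Patient A has no self-care and is confined to bed. Patient B has limited self-care and spends most of the day in bed. Both are illustrations, since the protocol does not give baseline function. The table assumes that the event does not itself change the patient's function.

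| Patient | Event | WHO grade | General level | Difference |
|---|---|---|---|---|
| A | easily bearable | 4 | 1 | 4 − 1 = 3 |
| A | severe | 4 | 3 | 4 − 3 = 1 |
| B | easily bearable | 3 | 1 | 3 − 1 = 2 |
| B | severe | 3 | 3 | 3 − 3 = 0 |

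**Step 3: can the scale separate events?** For patient A the WHO grade is 4 for both events, a spread of 4 − 4 = 0. A is already at the top, so no event can raise the grade. For patient B the spread is also 3 − 3 = 0 unless the event worsens function, and then only one step (4 − 3 = 1) is left. The general scale gives 3 − 1 = 2 for either patient, provided its moderate and severe wording is read in the numbered order.

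**Step 4: does the printed alignment hold?** The table pairs level 1 with grade 1. Grade 1 presupposes a patient who walks and works. An easily bearable event in patient A is level 1 on one row and grade 4 on the other, so the pairing fails for such a patient.

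**Step 5: where the grades are used.** Section 11.3.4.1 plans a listing and an incidence of adverse events and names no analysis by grade. The seriousness definition in 12.1 (4) does not refer to the grades. Section 12.3.1 gives fever its own grades. The grades of 12.3.2 therefore reach the recorded and reported severity of other signs, and no stated endpoint.

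**The case against.** The strongest reply is that the WHO wording is only one option. Section 12.3.2 gives it as an example, offers an event-based alternative, and covers subjective and objective signs alone. Fever is graded by temperature, and laboratory abnormalities are followed separately (8.2.13, 11.3.4.2). Death and life-threatening events are captured by the seriousness criteria in 12.1 (4), so a missing fatal level on the general scale loses little. Bleeding is documented in its own right (11.3.4.3). The general levels are numbered 1 to 3, so the intended order is clear even if the English is not. The contents also list Enclosure 5, criteria for adverse events, which is not in the text available and may hold event-specific grades.

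Most of this stands, and it limits the reach of the point. It does not remove the defect. The functional definitions are printed as permitted severity grades, either scale may be chosen, and numbering does not give the moderate and severe descriptions a usable boundary. Section 12.3.2 does not refer to Enclosure 5. Even if that enclosure holds sound criteria, the conflicting definitions would still be in force beside it.

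**Conclusion.** The point holds for subjective and objective signs. One of two interchangeable scales measures the patient, the other has a poorly drawn upper boundary, and the protocol does not say which applies. For a patient without self-care and confined to bed, the scales can differ by three grades for the same minor event.

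A reader might infer that every event in all 66 planned patients would be grade 4, so that severity carries no information. The documents do not support that. Fever is graded elsewhere, the general scale has no grade 4, and a patient with limited self-care fits grade 3. Baseline function is nowhere stated. That many patients would be at grade 4 is an assumption, plausible from the population in 6.1, and it could be any share.

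A reader might also tie these grades to the severe haemorrhage drop-out criterion in 10.1, and so to the per-protocol set. The protocol makes no such link.

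What is affected is the quality of recorded and reported severity, and no stated endpoint or analysis. Priority is low to moderate.

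**What to change.** In section 12.3.2, delete the functional grades as definitions of severity, together with the table that aligns them with the general levels. Name one event-based severity scale for all subjective and objective adverse events, to be used in both arms, with levels whose wording is clearly ordered and does not depend on walking, work or daily life. If Enclosure 5 already contains such criteria, refer to it and make it the only scale. Align the severity field of the case report form.

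The cost is one rewritten subsection and one form field. No added visit, assessment or patient is needed, and no rule for treating patients changes.

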### 12.4 Cause-and-effect relationship with the study medication

When adverse event occurs, the researcher should classify the event as follows, and if necessary, the opinion of principal investigator is added.

① Definitely related

- The evidence over administration of medication in question is present.
- The medication in question is the most compelling reason of adverse event compared to other possible reason.

- The adverse event is resolved with discontinuation of the medication in question.
- The adverse event is reproduced after rechallenge test (done when it is possible).
- The adverse event is consistent with the information known about the medication in question or medication of same sorts.

② Probably related

- The evidence over administration of medication in question is present.
- The time sequence between the administration of the medication and adverse event is reasonable.
- The medication in question is the most compelling reason of adverse event compared to other possible reason.
- The adverse event is resolved with discontinuation of the medication in question.

③ Possibly related

- The evidence over administration of medication in question is present.
- The time sequence between the administration of the medication and adverse event is reasonable.
- The medication in question is similarly compelling reason of adverse event compared to other possible reason.
- The adverse event is resolved with discontinuation of the medication in question.

④ Probably not related

- The evidence over administration of medication in question is present.
- There is other reason that explains the adverse event which is more compelling.
- The adverse event is not resolved or ambiguously resolved after discontinuation of the medication in question.

⑤ Definitely not related

- There is no evidence that the medication in question is administered.
- There is other reason for the adverse event that is most compelling.
- The adverse event is not resolved with discontinuation of the medication in question.

⑥ Unknown

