#### (2) Adverse drug reaction (ADR)

“Adverse drug reaction” is a reaction that has reasonable doubt that the medication and the reaction that has cause-and-effect relationship, or at least the possibility is not ruled out.

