## 12.5 Reporting method

### 12.5.1 Reporting the adverse event

- Principal investigator should inform the researcher, patients or legal guardian of possible adverse events and education the researchers to document all events that occur after administration of study medication.
- The systemic or clinicopathologic signs after administration of study medication is documented and stored to data sheets according to clinical study management regulation including the characteristics, event time, severity, management, treatment medication, duration, cause and effect relationship between the study medication.
- Principal investigator should describe and evaluate all sign/symptoms during clinical study when reporting study result. When serious adverse drug reaction occurs during the clinical study, principal investigator should report to IRB and decide continuance or discontinuation of the study. When prompt report is necessary due to following incidence, the funder should promptly report to the incidence to Korean food and drugs administration.
- “Serious adverse drug reaction” is a sign that cannot be excluded as a result of study medication administration and include following conditions.
  - ① Patient’s death during the study
  - ② When the patient’s life is threatened
  - ③ When lasting or significant disability or functional deterioration occurs
  - ④ When the patient needs hospitalization or delay in discharge when already hospitalized.
  - ⑤ When the medication causes congenital deformity or abnormality
  - ⑥ Other medically significant circumstances
- Additional safety information should be periodically reported until the adverse event is resolved (when the adverse event is resolved or impossible to follow up).
- Principal investigator should follow declaration of Helsinki regarding all matters.

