## (3) Report timing

When serious and unanticipated adverse drug reaction occurred during the clinical study, principal investigator is obligated to report the matter to IRB to evaluate continuance or discontinuation of the study, and the client is obligated to report the matter to Korean food and drugs administration within given period in each section.

- ① Adverse drug reaction which is not anticipated and cause death or threatens life is needed to promptly be reported. The client is obligated to report to Korean food and drugs administration as soon as possible by phone, fax or document within 7 days. Full written document is needed to be submitted within 15 days after the client was informed.
- ② The client is obligated to report the adverse reaction within 15 days after the reaction was informed for other significant unanticipated adverse drug reaction

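### The causality scale in section 12.4 has no related grade that a fatal or irreversible reaction can meet, contrary to the protocol's own definitions of an adverse drug reaction

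*Protocol*

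**What the plan says.** Section 12.2 has causality graded in six categories, and section 12.4 directs the researcher to classify each event into one of them.

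- Definitely, Probably and Possibly related each include the item "The adverse event is resolved with discontinuation of the medication in question".
- Probably not related includes "The adverse event is not resolved or ambiguously resolved after discontinuation of the medication in question" and also "There is other reason that explains the adverse event which is more compelling".
- Definitely not related includes "The adverse event is not resolved with discontinuation of the medication in question" and also "There is no evidence that the medication in question is administered".
- Unknown has no criteria.

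The rechallenge item under Definitely related is qualified as applying only when feasible. The resolution item has no such qualifier in any grade. Section 12.4 does not say whether all items of a grade must be met.

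Elsewhere the protocol defines a drug reaction without reference to resolution. Section 12.1(2) counts a reaction where a causal link is reasonably suspected, "or at least the possibility is not ruled out". Section 12.5.1 says that a serious adverse drug reaction "is a sign that cannot be excluded as a result of study medication administration", and its list of serious outcomes includes death and lasting disability. On timing, section 12.5.2(3) states: "Adverse drug reaction which is not anticipated and cause death or threatens life is needed to promptly be reported".

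**The concern.** Whether an event clears when the drug is stopped is useful evidence only if that can be observed. It cannot be observed after a death or a permanent deficit. It may also not be observable while the infusion runs, and sections 7.2.3 and 8.2.10 continue the infusion until CRRT ends. By requiring resolution even for Possibly related, the weakest related grade, section 12.4 closes the related side of the scale to the most serious outcomes. It also treats their irreversibility as a mark against the drug.

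What is at stake is safety reporting. The investigator's report to the IRB (12.5.1, 12.6(1)), the researchers' notice to the principal investigator and client (12.6(2)), the client's report to the regulator (12.6(4)) and the 7- and 15-day limits (12.5.2(3)) are all worded in terms of adverse drug reactions. Section 12.4 is the only tool the protocol gives for judging causality, so a scale narrower than the definition can leave events unrecognised as drug reactions.

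**Working it through.** The protocol states no figure on this point, so the check is one of logic. The criteria of section 12.4 were enumerated for a patient who received the drug.

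**Inputs.** Two items separate the grades for a treated patient: how compelling the drug is as a cause compared with the alternatives (most, similarly, less), and whether the event resolved after stopping. Every listed item of a grade is taken as required. The time-sequence, rechallenge and consistency items are assumed satisfied, which favours the related grades.

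| Drug as cause | Resolved | Not resolved |
|---|---|---|
| Most compelling | Definitely or Probably related | no graded category fits; Unknown |
| Similarly compelling | Possibly related | no graded category fits; Unknown |
| Less compelling | no graded category fits; Unknown | Probably not related |

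**Reading the table.**

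1. In the not-resolved column, 0 of the 3 related grades can be reached, however strongly the drug is suspected.
2. An unresolved event meets Probably not related only when another cause is also more compelling, because that grade lists both items.
3. Definitely not related is never met by a treated patient, because it lists absence of evidence that the drug was given.
4. So an unresolved event with the drug as the most or a similarly compelling cause ends in Unknown.

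**Comparison with the definitions.** Take a fatal event for which the drug is a similarly compelling cause. Under 12.1(2) the possibility of a causal link is not ruled out, so it is an adverse drug reaction. Under 12.5.1 the link cannot be excluded and death is a listed outcome, so it is a serious one. Under 12.4 it cannot be graded even Possibly related. The three sections do not give the same answer for the same event.

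**Sensitivity to the reading.** If the assessor lets the resolution item decide alone, the same event becomes not related. If the assessor picks the closest match, it fulfils 3 of the 4 items of Possibly related (administration, timing, similar weight as a cause) and 2 of the 3 items of Probably not related (administration, non-resolution), so 0.75 against 0.67. The text permits all three readings, and they lead to three different grades.

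**The case against.** The strongest reply is that reporting does not depend on section 12.4. No reporting rule names a grade. Sections 12.1(2) and 12.5.1 define reactions by whether a link can be excluded, and 12.5.2(2) lists serious and unexpected adverse events without a causality condition. An event graded Unknown is, on ordinary reading, not excluded and hence reportable. This stands to the extent that missed reporting is a risk and not a stated result. It does not remove the contradiction, because the timing rules in 12.5.2(3) speak only of adverse drug reactions and nothing says how Unknown is to be treated.

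A second reply is that stopping the drug can often be observed: section 9.1 foresees tapering or stopping it when reactions or bleeding occur. That helps for reversible events but not for death or permanent injury.

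Four stronger readings are tempting, and the documents do not support them.

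- A reader might infer that fatal reactions are automatically sorted into not related. The other items of those two grades prevent this unless the resolution item is weighed alone.
- A reader might take a cerebral bleed as the case that escapes the 7-day rule. Section 9.1 describes aggravated haemorrhage as a known effect, so a bleed may fall outside a rule for unanticipated reactions whatever its grade.
- A reader might multiply 33 patients by the assumed 50% mortality and report 16.5 affected deaths. Those are all-cause deaths under the assumption in 6.3.2, not suspected reactions.
- A reader might conclude that the drug's safety will be overstated in the results. Section 11.3.4.1 charts all adverse events and calculates their incidence without restricting to related ones, bleeding is recorded separately (8.3.2, 11.3.4.3), and ICU death is the primary endpoint regardless of grade.

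**Conclusion.** The point holds as an internal contradiction. With every listed item required, no related grade is open to a fatal or irreversible reaction, although 12.1(2) and 12.5.1 would call it an adverse drug reaction. Such an event falls to an undefined Unknown, or to a mistaken not-related grade. The conclusion rests on that reading of the lists. A closest-match reading could still reach a related grade, but the protocol does not prescribe one.

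No count of affected events can be given, because the documents contain no rate of suspected fatal or irreversible drug reactions. The 50% mortality assumed in 6.3.2 shows only that death will be a common outcome to assess. The efficacy analysis is untouched. The defect should be fixed, preferably before events are graded, but it does not by itself undermine the trial.

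**What to change.** Reconcile section 12.4 with 12.1(2) and 12.5.1 by three changes of wording:

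1. In the related grades, apply the resolution item only where the effect of stopping can be judged, and say that it is set aside after death, for an irreversible event, or where the drug was continued.
2. State that non-resolution of a fatal or irreversible event does not count towards Probably or Definitely not related.
3. State that an event whose relation to the drug cannot be excluded, including one graded Unknown, is handled as an adverse drug reaction for the reports under 12.5 and 12.6.

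It would also help to say whether all items of a grade must be met. The changes need no new data collection, visits or patients. The downside is a few more events graded related or reported.
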